## Methods/design

### Design

This study is a randomised controlled trial using three-groups: (1) Regional and remote intervention group, (2) Regional and remote control group, and (3) Metropolitan control group. Families will be classified as either metropolitan or regional and remote based on the ARIA+ score using the post code of the family's primary place of residence. Regional and remote families will be randomly allocated either to the intervention (1), or to a usual support control group (2). Metropolitan patients will receive support via traditional means as an additional usual support control group (3). This group will be used to provide a comparator against which the support provided to the regional and remote families can be judged.

The protocol for this study is registered with the Australian Clinical Trials Registry (ACTRN 012606000487516) and has been approved by the Royal Children's Hospital and Health Service District Ethics Committee and the University of Queensland Behavioural and Social Sciences Ethical Review Committee.

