### Data analysis

#### Sample size calculations

A total of 162 participants will be included in the study (based on data provided by the tertiary paediatric oncology referral centre this is feasible for a 24-month trial with a 20% refusal/attrition rate), 108 in the control group – 54 metropolitan and 54 regional and remote, and 54 in the regional and remote intervention group. Sample size calculations are given for the two main comparisons and economic analyses:

1. Regional and remote intervention group vs regional and remote usual support control group

- To test whether the provision of videotelephones to families in regional and remote areas can improve the health related quality of life of parents caring for a child with cancer over usual care, a unpaired t-test of the mean difference will be used [38]. This will be based on the SF-12 at week 12.

- As no paediatric caregiver research using the SF-12v2 has been undertaken in Australia to date, published evidenced available on paediatric parental caregiver burden in the US [39] and US norms [31] (Table 2) have been used as a guide for the sample size calculation. A clinically important difference would be to improve mean mental health related quality of life of parents (SF-12 Mental Component Summary [MCS]) in the intervention group by 7.5 points. This figure is further supported by calculation of SF-12v2 standard error of measurement [SEM], calculated as the standard deviation of an instrument multiplied by the square root of one minus its reliability coefficient [40]. With an SD of 10 and reliability coefficient of 0.86 [31], the MCS-12 has an SEM of 3.74. Evidence by Wywrich [41] supports the use of one SEM as an approximation of the *minimal *clinically important difference [MCID] of a psychometric instrument. Using this approximation, an improvement in MCS-12 of 7.5 represents two times the MCID, which is a large clinically important difference.

**Table 2 T2:** Published evidence available on the SF-12 health-related quality of life instrument.

Context	n	Details	Mean	SD
The impact of paediatric tracheotomy on parental caregiver burden and health status (US)[39]	154	PCS-12 MCS-12	50.5 35.8	11.3 11.4
US Norms[31]	7069	General US population		
		PCS-12	49.63	9.91
		MCS-12	49.37	9.75
		Depression		
		PCS-12	45.55	11.71
		MCS-12	37.40	10.76

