- Based on an improvement in MCS-12 mean in the intervention group of 7.5, and using SF-12v2 norm-based scoring methods (US general population SF-12v2 mean of 50 and SD of 10 [31]), at a power of 90% and a two-sided significance level of 1%, a sample size of 108 will be required, i.e. 54 in the intervention group and 54 in the control group.

2. Regional and remote intervention group vs metropolitan usual support control group

- To test whether the provision of videotelephones to families in regional and remote areas can improve the mental health related quality of life of parents to a level equivalent to that of metropolitan families receiving usual support, a test of equivalence will be used (according to the equivalence method described by Matthews [42]).

- With a two-sided significance level of 1%, sample size of 54, a mean difference between groups of zero and an equivalence bound of plus/minus 7.5, the study has a power of 87.2% for finding a genuine equivalence.

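### Comparison 2 aims to show improvement to metropolitan level, but its equivalence test cannot show improvement and no rule ties it to comparison 1

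*Protocol article*

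**What the plan says.** The protocol article has three groups: regional and remote families with videotelephone support (group 1), regional and remote families with usual support (group 2) and metropolitan families with usual support (group 3). Only groups 1 and 2 are randomised. Of group 3 the Design section says: "This group will be used to provide a comparator against which the support provided to the regional and remote families can be judged".

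The Sample size calculations section opens: "Sample size calculations are given for the two main comparisons and economic analyses". Comparison 1 is group 1 against group 2: an unpaired t-test on the SF-12 at week 12, planned on a 7.5-point improvement in the mental component summary (MCS-12), SD 10, two-sided 1% and 90% power. Comparison 2 is headed "Regional and remote intervention group vs metropolitan usual support control group". Its aim is to test whether videotelephones "can improve the mental health related quality of life of parents to a level equivalent to that of metropolitan families receiving usual support", and the method is a test of equivalence. For 54 families per group, a 1% level described as two-sided and no true difference, the power statement is: "an equivalence bound of plus/minus 7.5, the study has a power of 87.2% for finding a genuine equivalence".

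Hypothesis 2 is worded differently: videotelephone support for regional families will be as effective as traditional support for metropolitan families. The Statistical analysis section plans intention-to-treat comparisons between randomised groups and then longitudinal methods. Neither section orders the two comparisons, makes one conditional on the other, or says how a mixed result is to be read.

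**The concern.** The aim of comparison 2 has two parts: parents improve, and they reach metropolitan level. The test addresses only the second. Group 1 can match group 3 because videotelephony closed a deficit, or because there was little or no deficit to close. Group 2 separates these explanations, and comparison 2 does not use it.

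At stake is a mixed result: no benefit over regional usual support in comparison 1, equivalence with metropolitan families in comparison 2. Taken at its stated aim, comparison 2 would then count as evidence that videotelephony raised parents to metropolitan level, although the randomised comparison gave no support for any improvement. If the regional deficit is small, this is the most likely result for a service that does nothing.

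**Working it through.** **Inputs.** From Sample size calculations: 54 per group, SD 10, margin ±7.5, significance level 1%, planned effect 7.5, and a minimal clinically important difference (MCID) of 3.74 (one standard error of measurement). The regional deficit under usual support, g, is not in the article. It is an assumption, varied from 0 to 7.5 points.

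**Reproducing the plan's figures.**
- Standard error of a difference: 10 × √(2/54) = 1.925.
- Comparison 1: t-test power at 54 per group is 89.6% (normal approximation 90.7%), which agrees with the stated 90%.
- Comparison 2: with two one-sided t-tests at 1% per side, the critical value on 106 degrees of freedom is 2.362. Equivalence is declared when the observed difference is roughly within 7.5 − 2.362 × 1.925 = 2.95 points of zero. Simulation with estimated SDs (2 million runs) gives 87.2% at a true difference of zero, exactly the stated power. Reading the level as a 99% interval (0.5% per side) gives 79.3%, so the stated figure corresponds to 1% per side.

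**A videotelephone with no effect.** Group 1 then has the same true mean as group 2, so group 1 minus group 3 equals −g. Approximately,

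P(pass comparison 2) = Φ((2.95 − g)/1.925) − Φ((−2.95 − g)/1.925).

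At g = 3 this is about Φ(−0.03) − Φ(−3.09) = 0.49. The simulated values are:

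| Assumed deficit g (points) | Passes comparison 2, 1% per side | Same, 99% interval | Passes comparisons 1 and 2 (1% per side for equivalence) |
|---|---|---|---|
| 0 | 87% | 79% | 0.28% |
| 1 | 82% | 74% | 0.38% |
| 2 | 68% | 58% | 0.44% |
| 3 | 49% | 39% | 0.46% |
| 3.74 (MCID) | 35% | 26% | 0.43% |
| 5 | 15% | 10% | 0.33% |
| 7.5 | 1% | 0.5% | 0.07% |

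At g = 0 the inert pass rate is the protocol's own stated power. Of that 87.2%, about 87.2 − 0.3 = 86.9 percentage points fall where comparison 1 shows no benefit. The last column cannot exceed 0.5%, because an inert service wins comparison 1 in the beneficial direction only 0.5% of the time.

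**Power of the joint claim when the gap really is closed** (group 1 equal to group 3, group 2 lower by the gap; equivalence at 1% per side, superiority at two-sided 1%):

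| Gap closed (points) | Equivalence alone | Comparison 1 alone | Both |
|---|---|---|---|
| 7.5 | 87% | 90% | 79% |
| 5 | 87% | 49% | 43% |
| 3.74 | 87% | 25% | 21% |

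The loss at smaller gaps comes from comparison 1, which was sized for 7.5 points.

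**The case against.** The strongest reply is that improvement is tested elsewhere. Comparison 1 is randomised, listed first, on the same scale and powered at about 90%. This stands. A reader might infer that the trial's whole case for improvement rests on equivalence with metropolitan families; the article does not support that. The defect is confined to comparison 2's stated aim and the missing link to comparison 1.

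Second, the article contains no rule that equivalence alone will be reported as proof of improvement, and hypothesis 2 claims only equal effectiveness, for which group 1 against group 3 is a natural contrast. This also stands: the misreading is left open, not prescribed.

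Third, gating and supporting contrasts are commonly left to an analysis plan, and calling two comparisons main does not exclude others. The Design section's wording on the metropolitan comparator could cover group 2 as well. So the absence of a listed group 2 against group 3 contrast is not in itself a fault. What remains is in the article's own text: a stated aim paired with a test that cannot answer it.

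Fourth, the size depends on the assumed deficit and on the margin. If the planned 7.5-point improvement is taken as the full regional deficit, the inert pass rate is only 1%. At zero deficit, a margin of 5 would cut it from 87% to 19%, and a margin of 3.74 to about 0.02%. The logic does not depend on the margin; the magnitude does.

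**Conclusion.** The point holds for comparison 2. Equivalence of group 1 with group 3 cannot show that parents improved, and the article does not tie the claim to comparison 1, which can. On the protocol's inputs the inert pass rate is 49% or more for regional deficits up to 3 points, 35% at the protocol's MCID, 15% at 5 points and 1% at 7.5. These figures assume equal SDs of 10, 54 analysed per group, 1% per side and no confounding between regional and metropolitan families.

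Two stronger readings should be avoided. It is not certain that an ineffective service would be found equivalent; that depends on a deficit the article does not give. Nor would similarity of groups 2 and 3 cancel a significant comparison 1: a non-randomised contrast with a wide margin should not override a randomised superiority result.

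**What to change.** 1. State that improvement to a level equivalent to metropolitan families is concluded only if comparison 1 shows superiority of group 1 over group 2 and comparison 2 shows equivalence of group 1 with group 3.
2. If only comparison 2 succeeds, report equivalence with metropolitan families without attributing it to videotelephony.
3. Report group 2 against group 3 on week-12 MCS-12 descriptively, with its confidence interval, as the benchmark for whether a deficit existed. It must not override a significant comparison 1. If that interval also lies within ±7.5, credit improvement over usual support but withhold the statement that families were raised to metropolitan level.

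This needs no new data: a conclusion rule and one further contrast. The price is power for the joint claim: about 79%, 43% and 21% when gaps of 7.5, 5 and 3.74 points are fully closed, against 87% for equivalence alone. The withholding clause in item 3 takes off up to about 1.3 percentage points more (simulated under the same assumptions). The loss should be stated beside the rule, because at gaps well below 7.5 points the trial is unlikely to win the joint claim even if the service works.

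### The 87.2% equivalence power belongs to two one-sided tests at 1% each (98% CI); at the stated two-sided 1% level it is about 79%

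*Protocol article*

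**What the plan says.** The section on sample size names two main comparisons and allocates "108 in the control group – 54 metropolitan and 54 regional and remote, and 54 in the regional and remote intervention group".

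Comparison 1 (intervention against regional and remote usual support) is an unpaired t-test of superiority. Its sample size is calculated "at a power of 90% and a two-sided significance level of 1"%, using norm-based scoring ("US general population SF-12v2 mean of 50 and SD of 10") and a difference of 7.5 points.

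Comparison 2 (intervention against metropolitan usual support) is the test of Hypothesis 2. The method is given by citation: "a test of equivalence will be used (according to the equivalence method described by Matthews [42"]). Its conditions are "With a two-sided significance level of 1%, sample size of 54, a mean difference between groups of zero" and bounds of ±7.5 points, and the article concludes that "the study has a power of 87.2% for finding a genuine equivalence". No confidence level for the interval and no level for each one-sided test is given, and the SD is not restated.

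**The concern.** Equivalence is normally shown by two one-sided tests, one against each bound. A quoted level of 1% can then mean 1% per test (98% interval) or 0.5% per test (99% interval). The phrase used for comparison 2 is the one used for comparison 1, where it means 0.5% in each tail. If it keeps that meaning, the quoted power is too high.

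More than a power figure is at stake. The significance phrase is the only statement in the article from which the pass/fail rule for equivalence can be read. If the phrase and the power point to different rules, the choice between them could be made after the data are seen.

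**Working it through.** **Inputs**

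- n = 54 per group, true difference 0, bounds ±7.5, stated power 87.2%: comparison 2 and the allocation sentence.
- SD = 10: stated for comparison 1. Carrying it over to comparison 2 is an assumption.

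**Standard error**

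SE = 10 × √(2/54) = 1.9245, with df = 2 × 54 − 2 = 106. The bound in SE units is 7.5 / 1.9245 = 3.897.

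**Power for comparison 2**

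Equivalence is concluded when the observed difference ± t × (estimated SE) lies inside ±7.5. By normal approximation, with true difference 0, power = 2Φ(7.5/SE − z) − 1. The exact figure uses the t critical value and integrates over the sampling distribution of the pooled variance.

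- Normal approximation, 1% per test: 2Φ(3.897 − 2.326) − 1 = 2Φ(1.571) − 1 = 88.4%.
- Normal approximation, 0.5% per test: 2Φ(3.897 − 2.576) − 1 = 2Φ(1.321) − 1 = 81.4%.

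| Level per one-sided test | Interval | t critical value (106 df) | Power, normal | Power, exact t |
|---|---|---|---|---|
| 1% | 98% | 2.362 | 88.4% | **87.2%** |
| 0.5% | 99% | 2.623 | 81.4% | **79.2%** |

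The exact figure at 1% per test (87.17%) reproduces the stated power to the printed decimal. Solving for the per-test level that gives 87.2% returns 1.00%. A simulation of 2,000,000 trials gave 87.16% and 79.2% for the two rules.

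**What the phrase means in comparison 1**

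At 54 per group and a difference of 7.5, the unpaired t-test with 0.5% per tail has power 89.6% (90.7% by normal approximation), which agrees with the stated 90%. With 1% in a single tail it would be 93.6%. So in comparison 1 the phrase means 0.5% per tail.

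**Could another input explain it?**

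- With the general-population MCS-12 SD of 9.75 from Table 2, 0.5% per test gives 82.6% (exact) to 84.5% (normal).
- To reach 87.2% at 0.5% per test, the SD would have to be about 9.4 (exact) to 9.5 (normal). The article gives no such value.
- To reach 87.2% at 0.5% per test with SD 10 takes about 62 per group: 61 gives 86.9% and 62 gives 87.7%.

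**Effect on the decision**

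The largest observed difference that still counts as equivalent, if the observed SD is 10:

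- 98% interval: 7.5 − 2.362 × 1.9245 = 7.5 − 4.546 = 2.95 points.
- 99% interval: 7.5 − 2.623 × 1.9245 = 7.5 − 5.048 = 2.45 points.

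**The case against.** The strongest reply is that the power is sound and only a word is loose. Two one-sided tests at 1% each have an overall false-equivalence rate of 1% (simulated 1.0% at the bound). The level of 1%, 54 per group, ±7.5 and 87.2% therefore fit together as a 1% equivalence test, and the term two-sided may merely mean that both bounds are tested. The 99% interval is stricter than a 1% rate requires. The cited method may also fix the convention, and it is not available to check. Finally, 87.2% did not determine the sample size, the comparison with metropolitan families is not randomised, and the rules disagree only over a band of 0.5 points.

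Much of this stands. The 98% rule is legitimate, the exact match suggests it is what was calculated, and the fault may lie in the label. The consequences for design are modest.

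It does not remove the conflict. In one section the same phrase means 0.5% per tail for one main comparison and has to mean 1% per test for the other, and nothing in the text tells the reader so. Nor is this detail left to an analysis plan: the article prints both the level and the power, and they do not agree.

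**Conclusion.** The point holds. As worded, the level for comparison 2 gives a power of 79.2% (81.4% by normal approximation), not 87.2%, a shortfall of 6 to 8 percentage points. The printed power is correct for a different rule, 1% per one-sided test. Which of the two was intended cannot be settled from the article.

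This rests on an SD of 10 carried over from comparison 1, which the exact match at 1% per test supports, on 54 analysed per group, and on reading the significance phrase as comparison 1 uses it. It needs correcting because it governs the decision rule for one of the two main comparisons. It does not undermine the sample size, which was derived from comparison 1.

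**What to change.** Choose one rule before any outcome data are examined, and state it with its own power:

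- **(a)** Equivalence is concluded if the 99% confidence interval for the difference lies wholly within ±7.5 points; power about 79% with 54 per group and SD 10. This keeps the meaning used in comparison 1. To retain 87.2% under this rule would take about 62 per group.
- **(b)** Equivalence is concluded if two one-sided tests, each at 1%, both reject, that is, if the 98% confidence interval lies within ±7.5 points; power 87%. The two-sided 1% wording is deleted from comparison 2.

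In either case, state the SD of 10 for this comparison. The cost is one sentence and no change to conduct. Under (a) the reported power falls by 8 points; under (b) no figure changes.

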### Hypotheses

1. Videotelephony will be a feasible and acceptable mode of service delivery to regional and remote paediatric oncology families

2. Support provided using videotelephony to regional and remote paediatric oncology families will be as effective as support provided via traditional mechanisms to metropolitan families

3. Using videotelephony will be a cost-effective method of service delivery.

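### The equivalence bound of plus/minus 7.5 is two MCIDs on the protocol's own scale, so a positive test leaves open a deficit of one to just under two MCIDs and cannot alone support a claim of equal effectiveness

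*Protocol article*

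**What the plan says.** Hypothesis 2 (Hypotheses) reads: "Support provided using videotelephony to regional and remote paediatric oncology families will be as effective as support provided via traditional mechanisms to metropolitan families". Its only stated test is comparison 2 under Sample size calculations, an equivalence test of the intervention group against the metropolitan usual-support group. The design figures are "With a two-sided significance level of 1%, sample size of 54", "a mean difference between groups of zero and an equivalence bound of plus/minus 7.5", and the result is that "the study has a power of 87.2% for finding a genuine equivalence". The allocation is "54 metropolitan and 54 regional and remote, and 54 in the regional and remote intervention group".

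Under comparison 1 the same section puts 7.5 on a clinical scale. It states: "With an SD of 10 and reliability coefficient of 0.86 [31], the MCS-12 has an SEM of 3.74". It takes one SEM as an approximation of the MCID and concludes that "an improvement in MCS-12 of 7.5 represents two times the MCID, which is a large clinically important difference". There 7.5 is the improvement the intervention is meant to achieve over regional usual support. Comparison 2 gives no separate reason for using 7.5 as an equivalence bound.

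**The concern.** An equivalence bound marks the largest difference one is prepared to regard as unimportant. Here one number serves as a large, important difference in comparison 1 and as the limit of equivalence in comparison 2.

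Comparison 2 is one of two main comparisons, and a positive result would be read as showing that videotelephone support brings regional parents level with metropolitan parents. The test would in fact show only that the two groups do not differ by as much as 7.5 points. A shortfall above the protocol's MCID, or nearly as big as the full target benefit, would remain compatible with a positive result. The margin, alpha, sample size and power are all fixed in the article, so this is not a detail left to an analysis plan.

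**Working it through.** **Inputs.** Margin 7.5 and true difference 0 (comparison 2); 54 per group; alpha 1%; reliability 0.86 and SD 10 (comparison 1). Comparison 2 states no SD. I carry over SD 10 as an assumption ("US general population SF-12v2 mean of 50 and SD of 10") and also use 11.4, the caregiver MCS-12 value in Table 2.

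**Margin on the protocol's scale.** SEM = 10 × √(1 − 0.86) = 3.74, and 7.5 / 3.74 = 2.0 MCIDs.

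**Reproducing the stated power.** The standard error of the difference is 10 × √(2/54) = 1.925. Two one-sided t-tests on 106 degrees of freedom, true difference 0:
- 1% per one-sided test: exact power 87.2%, as stated (normal approximation 88.4%).
- 0.5% per one-sided test: exact power 79.2% (normal approximation 81.4%), which does not match.

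The stated figure therefore corresponds to SD 10 and a 98% confidence interval lying inside plus/minus 7.5. The power arithmetic is sound under that reading.

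**What a positive result looks like.** At SD 10 the half-width of the 98% interval is 2.362 × 1.925 = 4.55. Equivalence is declared when the observed difference is within 7.5 − 4.55 = 2.95 points. At that limit the interval reaches 7.5.

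**Chance of declaring equivalence when the intervention group is truly worse** (exact t, 54 per group, margin 7.5):

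| True deficit | SD 10, 1% per side | SD 10, 0.5% per side |
|---|---|---|
| 3.74 (one MCID) | 34.5% | 25.6% |
| 5 | 14.8% | 9.7% |
| 6 | 6.0% | 3.5% |
| 7.5 (two MCIDs) | 1.0% | 0.5% |

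With SD 11.4 the figure at 3.74 is 26% (1% per side) or 18% (0.5% per side). The range at one MCID is thus 18% to 35%.

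**Power against plus/minus 3.74** (SD 10, true difference 0, 54 per group): 0.02% at one-sided 1%, because the half-width of 4.55 already exceeds 3.74 at the planned SD; about 23% at one-sided 5%. By normal approximation, 80% power at one-sided 1% would need about 187 per group.

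**The case against.** A reader might infer that equivalence could be declared with a large deficit still open. The documents do not support that. The article applies the word large to 7.5, and a positive test excludes 7.5 at its error rate: the chance of declaring equivalence at that true deficit is 1%. What stays open is the band from one to just under two MCIDs.

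The test is also stricter than the margin alone suggests. At the planned SD, an observed deficit of one MCID would not pass, since the limit is 2.95 points. At a true deficit of 3.74 the test fails about 65% of the time, and at 6 points about 94%. This stands, and it limits the size of the problem, but it does not change what a positive result can be said to exclude.

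The benchmark of 3.74 is soft: the article offers one SEM as an approximation and nowhere states that a group difference of that size rules out equivalence. So the documents do not make plus/minus 3.74 the only admissible margin, and an intermediate one could be argued. Yet the article relies on this approximation to show that 7.5 is large, and it gives no other ground for 7.5 as a bound.

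Finally, the metropolitan group is a non-randomised benchmark and the bound is stated openly. Randomised comparison 1 and the cost-effectiveness analysis, which uses the regional control group, are untouched. That is correct, and it confines the problem to hypothesis 2 and comparison 2.

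**Conclusion.** The concern holds in this form. The bound is two MCIDs by the protocol's own account and equals the full benefit sought in comparison 1. Success would exclude a deficit of 7.5 or more but not one between 3.74 and just under 7.5, so it cannot by itself establish that the support is as effective or that the groups are equivalent.

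On the reading that reproduces the stated power (SD 10, 1% per one-sided test), a true one-MCID deficit is declared equivalent 35% of the time and a 5-point deficit 15%. The 35% is the top of an 18% to 35% range over SD 10 or 11.4 and 0.5% or 1% per side. The conclusion about the margin rests only on the article's own MCID and does not depend on the SD assumed for comparison 2 or on how alpha is split.

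**What to change.** Keep the sample size and the test, and change what they are said to show:

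- In hypothesis 2 and comparison 2, state that success at plus/minus 7.5 means only that a large, two-MCID difference has been excluded.
- Report the difference with its confidence interval against both 3.74 and 7.5.
- Do not describe the result as equivalent or equally effective without that qualification, unless the interval lies inside a bound that the protocol itself regards as unimportant. If such a bound is wanted, name and justify it before results are known.
- State that at plus/minus 3.74 the present size has almost no power (0.02% at one-sided 1%, about 23% at one-sided 5%), so that failure to meet that bound is not read as evidence of a difference.

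The edits are to wording plus one reported interval. The real cost is a weaker headline claim for comparison 2: at 54 per group and the 1% level, an unqualified claim at the MCID is practically out of reach.
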